### Outpatient chronic low back pain physiotherapy specialist area

#### Procedures

The sample will consist of participants who had been assessed as being suitable for group exercise classes, after having completed individual face-to-face physiotherapy sessions. A similar procedure as for arthroplasty telerehabilitation session will be followed for the above cohort of patients. The telerehabilitation session will follow an adapted framework of questions, which will explore the patient’s functional ability, pain score and self-management principles (Appendix 2). At every session, the Keele STarT Back screening tool will be used as the outcome measure to monitor patient progress and to categorise patients as low, medium and high risk.

Following the first session of telerehabilitation, those patients who fall into the high-risk category will be called back for a face-to-face consultation session and managed accordingly. Patients who fall into the medium- and low-risk category will be managed via telerehabilitation, wherein a specific category or level of a HEP will be prescribed and sent to the patients via their preferred method of communication. Follow-up appointments will be at 2–4-week intervals. Based on the patients’ report and presentation, exercises and advice will be progressed. Once patients have reached a score of less than three on their Keele STarT Back screening assessment tool, they can be discharged from physiotherapy.

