#### Outcome measure

The Keele STarT Back screening tool is available in English and Zulu, and according to Bruyère et al. (2014) the test-retest reliability of the Keele STarT back screening tool total score was excellent with an intraclass correlation coefficient of 0.90. The validity was found to be moderate to high in Pearson’s correlation for questions three to nine and a low correlation for questions one and two (Bier et al. 2017). This tool is designed to screen primary care patients with low back pain and serves as a prognostic indicator for initial decision-making. This tool allows clinicians to group low back pain patients into three categories of risk.

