### Statistical analysis

All identifiers will be removed. Descriptive statistics will be used to analyse the gathered data during the time of the study. Frequencies and percentages for categorical data and means and standard deviations or medians and percentiles for numerical data will be calculated. The data will be tabulated; trends will be presented in the form of graphs. A statistician assisted with the planning of data analysis. The statistical analysis for each objective will now be presented:

1.To determine the effects of telerehabilitation services for patients who have orthopaedics conditions (arthroplasty).

Categorical variables (symptoms, pain, function and daily living, function, sports and recreational activities, quality of life) will be summarised by using frequencies and percentages. Bivariate analysis between groups for total hip replacements and total knee replacements will be performed by using Chi squared test if 25% of the expected frequencies are above five or by using Fisher’s exact test if the assumption is not valid. Similarly, bivariate associations between gender, age and compliance with the outcomes (symptoms, pain, function and daily living, function, sports and recreational activities, quality of life) will be assessed by using Chi squared test or Fisher’s exact test:

2.To determine the effects of telerehabilitation services for patients who have NMS conditions (chronic low back pain).

Categorical variables (symptoms, pain, function and daily living, function, sports and recreational activities, quality of life) will be summarised by using frequencies and percentages. Whilst age is a continuous/numerical variable and the outcomes being categorical variables, with three groups, an analysis of variance (ANOVA) test is used if data are normally distributed or Kruskal Wallis test is used if they are not normally distributed:

3.To determine the effects of telerehabilitation services for patients who have paediatric conditions.

Categorical variables will be summarised by using frequencies and percentages:

4.To determine the patient or caregiver and physiotherapist experiences in the rollout of telerehabilitation services.

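### Age is put through a chi-squared or Fisher test in arthroplasty, which forces unstated age bands, although the next item treats it as numerical

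*Protocol article*

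**What the plan says.** Both statements are in the Statistical analysis section of the protocol article.

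- **Item 1, arthroplasty.** The plan is to examine "bivariate associations between gender, age and compliance with the outcomes", and these "will be assessed by using Chi squared test or Fisher’s exact test". Age is listed with gender and compliance as if all three were categorical. No age categories are given.
- **Item 2, chronic low back pain.** Age is called numerical: "Whilst age is a continuous/numerical variable and the outcomes being categorical variables, with three groups, an analysis of variance (ANOVA) test is used" if the data are normal, and "Kruskal Wallis test is used if they are not normally distributed".

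Two other places bear on how far the point reaches.

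- The low back pain Procedures section says the screening tool is used "to categorise patients as low, medium and high risk", and the Outcome measure section that follows repeats that there are three risk categories. Item 2 speaks only of three groups and does not say that they are these.
- Methods and design leaves the sample size to a pilot study, so no number of patients is available for either condition.

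**The concern.** A chi-squared or Fisher test cannot take age in years. Someone must first decide how many bands to use and where to cut. That has two costs.

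- **Information.** Patients within a band are treated as the same age, and those just either side of a cut as different. A real association between age and outcome is then more likely to be missed.
- **Discretion.** Different cut-points give different p-values. With none fixed, the bands can be settled after the results are visible.

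The article itself removes any reason to accept these costs, because item 2 recognises age as numerical and names tests that use it so. Missing cut-points alone could be left to a fuller document. The finding is that the article fixes a test that needs bands in one item and contradicts that treatment of age in the next.

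**Working it through.** The article states no sample size, alpha, power or effect size for these tests, so there is no figure of its own to reproduce. Everything below rests on assumptions and shows only the order of the loss.

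**1. Cost of banding alone, analytically.** Assume two-sided alpha of 5%, normally distributed age, three outcome groups, and a median split.

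- A 1-df test that uses numerical age and an even trend has 80% power at noncentrality (1.960 + 0.842)² = 7.85.
- At that noncentrality, a 2-df ANOVA-type test on numerical age has about 71% power. For 80% it needs noncentrality 9.63, and 9.63 / 7.85 = 1.23.
- A median split keeps a fraction 2/π = 0.64 of the information. The noncentrality falls to 7.85 × 0.64 = 5.0, and the 2-df chi-squared test has about 50% power. For 80% it needs 1.23 × π/2 = 1.93 times the patients of the trend test.
- The comparison that isolates banding is between the two 2-df tests: 71% against 50% power, or 1.93 / 1.23 = 1.57. That is about 57% more patients to recover what the split discards.

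**2. Simulation with equal steps.** Assume groups of 50/35/15%, age 0.4 SD higher per step, 4,000 datasets per setting, two-sided 5%, and age split at the median for chi-squared.

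| n | ANOVA | Kruskal-Wallis | Chi-squared, banded age | ANOVA minus banded |
|---|---|---|---|---|
| 40 | 33% | 30% | 23% | 10 points |
| 60 | 47% | 44% | 31% | 16 points |
| 100 | 73% | 70% | 51% | 22 points |

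Independent re-runs at n = 60 gave 47–48% for ANOVA, 42–45% for Kruskal-Wallis and 31–32% for the banded test.

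**3. A different data-generating model.** Three ordered groups were drawn from a proportional-odds model, with N = 60, 100 or 150, log-odds 0.35, 0.5 or 0.7 per SD of age, and equal or 50/35/15% shares. Chi-squared on median or tertile bands was below both ANOVA and Kruskal-Wallis in every setting with a real effect.

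- Example (N = 100, equal shares, log-odds 0.5): ANOVA 65.5%, Kruskal-Wallis 63.2%, median split 44.7%, tertiles 43.9%. The median-split gap to ANOVA is 65.5 − 44.7 = 20.8 points.
- Smallest gap (N = 60, equal shares, log-odds 0.35): Kruskal-Wallis 20.7% against median split 16.9%, or 3.8 points, where every test is weak.
- Largest gap (N = 60, equal shares, log-odds 0.7): ANOVA 66.8% against tertiles 42.9%, or 23.9 points.

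**4. Other shapes.** When only the high group or only the middle group differed in age, the banded test again had less power than ANOVA and Kruskal-Wallis.

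**5. Validity.** With no age effect, all tests in step 3 rejected in 3.7% to 5.9% of runs. With bands fixed in advance, the cost is power and not a false-positive problem.

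**The case against.** **Age is peripheral.** Neither objective concerns age and the study is mainly descriptive, so no decision rests on this p-value. That stands, and it limits the weight of the point.

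**The power figures are not arthroplasty estimates.** They assume three outcome groups. Item 1 gives no levels for its outcomes, and the arthroplasty Outcome measures section describes the instruments as scores. That also stands. The figures are illustrative, but the direction held in every setting tried.

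**A reader might infer that the low back pain tests are also wrong,** because ANOVA and Kruskal-Wallis ignore the order of low, medium and high risk. The documents do not support this. The link between the three groups and the risk categories is an inference, and both tests are valid for an association between numerical age and a three-level variable. A trend test is a trade-off. At n = 60 with 50/35/15% groups it has about 54% power against 47% for ANOVA when age rises in equal steps. It has about 29% against 45% when only the high-risk group differs, and about 22% against 59% when only the middle group differs.

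**A reader might also infer that both conditions need an ordinal model so that their results can be compared.** No objective compares the two conditions and they use different instruments. Ordinal regression in arthroplasty would assume ordered levels that the article never defines. Nor does the article rule out estimates: it plans means, standard deviations, medians, percentiles, frequencies and percentages.

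**Conclusion.** The point holds for item 1. The article sends age to a test that requires categories, gives none, and in the next item calls the same variable numerical. Nothing elsewhere in the article reconciles the two.

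Under the assumed 50/35/15% groups, n = 60 and 0.4 SD per step, banding brings power down to about 30%, from about 45% for Kruskal-Wallis and 47% for ANOVA. Across the settings tried, the loss ran from about 4 points, where every test was weak, to about 24. A median split of normally distributed age costs roughly the same as needing 57% more patients. The exact size depends on a sample size, group shares and effect that the article does not state; the direction did not change in any setting.

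The point does not extend to ANOVA or Kruskal-Wallis in low back pain. Because age is a secondary variable here, this is a minor improvement, worth making because it costs nothing.

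**What to change.** In item 1, remove age from the variables tested by chi-squared or Fisher's exact test, leaving gender and compliance there. Analyse age as a numerical variable, as item 2 already does: ANOVA or Kruskal-Wallis across the outcome categories, or the two-group equivalent where an outcome has two levels. Report the difference in age between categories with a 95% CI alongside the p-value. If age bands are wanted for descriptive tables, state the cut-points before the data are examined.

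For low back pain no change is required. An ordered or trend method may be added if the three groups are confirmed as the risk categories and a steady change with age is expected. It gains about 5 to 10 points of power only if age rises roughly evenly across the groups, and can lose power otherwise.

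The cost is a change of analysis wording. No new data, visits or patients are needed.

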## Methods and design

Purposive sampling will be used for this prospective mixed method study. Patients who have previously attended the outpatient physiotherapy department for the management of their orthopaedic, NMS and paediatric conditions prior to the national lockdown and those who had to have their appointments cancelled will be invited to participate. These patients will be selected as they are long-term patients requiring ongoing physiotherapy to prevent further disability but are not prioritised for face-to-face consultations because of the COVID-19 pandemic. Initially, a pilot study will be conducted to determine the sample size and rule out any errors in the methodology, and thereafter the study will be expanded.

A standard operating procedure (SOP) will be developed for arthroplasty (orthopaedic) and patients with chronic low back pain (NMS), cerebral palsy, developmental delay and acute orthopaedic conditions (paediatrics) with the purpose of providing an outline for therapists to deliver telerehabilitation services effectively and ethically. For each area, a database will be created containing videos and images of relevant interventions related to the specific condition being treated. Exercise prescription will commence from the patients’ current level of function and will be progressed as per the criteria described in the section’s guidelines of management of arthroplasty, chronic low back pain and paediatric patients. A section on general advice and health education will also be included.

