Frequencies and proportions will be used to summarise categorical variables. The two samples proportions test will be used to compare if there are any differences between the Yes or No responses. Comparisons between proportions with categorical variables will be performed by using the Chi squared test with the condition that the assumption is met:

5.Qualitative information will be gathered from two sources. The therapist’s experiences will be collected as positive, negative, challenges and other, and if further subthemes emerge from those categories, it will be described verbatim. In the subjective framework of questions, patients are asked a directed open-ended question on their experience of the call and the telerehabilitation sessions. The responses will also be categorised into themes that emerge.

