**Table d31e1575:**

1.	Did you enjoy the experience of tele-rehab for you and your child?	Yes	No	N/A	Comments and/or Suggestions		
2.	Do you feel like you learnt better how to help your child during tele-rehab?	Yes	No	N/A	Comments and/or Suggestions		
3.	What was difficult for you during the tele-rehab calls and treatment?	Yes	No	N/A	Comments and/or Suggestions		
4.	Was your culture and language respected during the calls and treatment?	Yes	No	N/A	Comments and/or Suggestions		
5.	Was the therapist’s attitude friendly and caring towards you?	Yes	No	N/A	Comments and/or Suggestions		
6.	Were you able to use any of the videos or pictures that were sent to you?	Yes	No	N/A	Comments and/or Suggestions		
7.	Were you given the chance to ask questions about your child’s treatment?	Yes	No	N/A	Comments and/or Suggestions		
8.	Where you given the right to refuse tele-rehab treatment?	Yes	No	N/A	Comments and/or Suggestions		
9.	Do you feel your child has benefitted from the advice and exercises given during tele-rehab?	Yes	No	N/A	Comments and/or Suggestions		
10.	How likely are you to recommend tele-rehab to another parent?	Very low	Low	Not sure	High	Very high	Comment and/or suggestions:

## Appendix 6

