**Table d31e1731:**

Questions	1	2	3	4	5	Comments and/or Suggestions
1. Rate the effectiveness of the implementation of the tele-rehab						
2. Do you strive towards achieving the best physiotherapy practice while conducting tele-rehab?	Yes/No (Elaborate Please)					
3. How likely are you to recommend tele-rehab to other colleagues?	1	2	3	4	5	Comments and/or Suggestions
4. Name the two resources that will assist you in performing tele-rehab more efficiently.						
5. Do you feel that you are effective as a therapist during tele-rehab consultations?	1	2	3	4	5	Comments and/or Suggestions
6. Are you satisfied with your experience of tele-rehab overall?	1	2	3	4	5	Comments and/or Suggestions
7. Which skills (clinical and non-clinical) did you learn or develop to carry out tele- rehab more effectively?	Clinical: Non-clinical:					
8. Which of your skills (clinical and non-clinical) did you transfer (teach other staff) to aid in carrying out effective tele- rehab?	Clinical: Non-clinical:					
9. What protocols, procedures or logistics would help to provide more effective tele-rehab in future?						
10. Any other suggestions or comments?

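### The planned two-sample test of Yes against No treats shares of one sample as two independent samples and overstates the evidence for the experience items

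*Protocol article*

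**What the plan says.** The Statistical analysis section of the protocol article takes the experiences of patients, caregivers and physiotherapists as its fourth item. Categorical answers are first summarised by frequencies and proportions. Then: "The two samples proportions test will be used to compare if there are any differences between the Yes or No responses". The next sentence covers a different comparison: "Comparisons between proportions with categorical variables will be performed by using the Chi squared test with the condition that the assumption is met".

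The Yes/No data visible in the article come from two forms:

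- **Caregiver questionnaire (Appendix 5).** Items 1 to 9 offer Yes, No or N/A. Item 1 is typical: "Did you enjoy the experience of tele-rehab for you and your child". Item 3 has the same boxes but reads "What was difficult for you during the tele-rehab calls and treatment".
- **Therapist feedback form (Appendix 6).** One item, number 2, is answered Yes or No.

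The article gives no significance level or sidedness for this test and does not say how N/A answers are handled. Sample size is left open in Methods and design: "Initially, a pilot study will be conducted to determine the sample size and rule out any errors in the methodology".

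**The concern.** A two-sample test of proportions assumes that the two proportions come from independent groups. Here the sentence names the Yes and the No responses as the things compared, and names no groups of respondents. On one item, each person who says Yes is a person who does not say No, so the two proportions move in opposite directions. The test ignores that negative correlation and understates the variance of their difference.

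The error always runs the same way: p-values come out too small. Experience is the first of the two aims in the Objectives section, and this is the only named test of whether opinion leans one way. It could be repeated over as many as nine caregiver items. An item on which opinion is evenly split could be reported as significantly favourable or unfavourable more often than the nominal level allows.

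**Working it through.** The article states no error rate, sample size or power for this test, so there is no figure of its own to reproduce.

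**Inputs**

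- Test and what it compares: Statistical analysis, fourth item.
- One answer per respondent per item: Appendices 5 and 6.
- Significance level: assumed two-sided 5%; 1% and 10% are also shown.
- Number of answers n: not fixed, so a range is shown.
- N/A: first excluded, then kept in the denominator.

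**Large samples, N/A excluded.** Let p be the proportion Yes among n Yes/No answers, so the proportion No is 1 − p and the difference is 2p − 1. With opinion evenly split:

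- Variance assumed by the two-sample test: 2 × 0.25/n = 0.5/n.
- True variance: 4 × 0.25/n = 1/n.

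The true variance is twice the assumed one, so the test statistic has standard deviation √2 instead of 1. The actual false-positive rate is 2 × P(Z > 1.96/√2) = 2 × P(Z > 1.386) = 16.6%. The same formula gives 6.9% at a nominal 1% and 24.5% at a nominal 10%.

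**Exact rates.** Enumerating the binomial distribution with p = 0.5, for the pooled test at nominal 5%:

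| n | Planned test | One-sample exact binomial |
|---|---|---|
| 20 | 11.5% | 4.1% |
| 30 | 20.0% | 4.3% |
| 50 | 20.3% | 3.3% |
| 100 | 19.3% | 3.5% |
| 200 | 17.9% | 4.0% |
| 500 | 16.6% | 4.4% |

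Over every n from 20 to 300 the planned test ranges from 11.5% to 23.0%, with a mean of 16.6%. A continuity correction lowers it but does not repair it: 9.9% to 16.6% over the sizes examined, which ran from 10 to 1000.

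**N/A kept in the denominator.** If a share q answers N/A and the rest split evenly, the true variance of the difference is (1 − q)/n and the test assumes (1 − q)(1 + q)/(2n). The ratio is 2/(1 + q), and the rate is 2 × P(Z > 1.96/√(2/(1 + q))):

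- q = 10%: 14.6%
- q = 20%: 12.9%
- q = 30%: 11.4%

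**Worked example, 20 Yes and 10 No.** The difference is 20/30 − 10/30 = 0.333.

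- Planned test: standard error √(0.5/30) = 0.129, z = 2.58, p = 0.010.
- One-sample z test: standard error √(1/30) = 0.183, z = 1.83, p = 0.068.
- One-sample exact binomial test: p = 0.099.

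The step from 0.010 to 0.068 is due to the wrong standard error. The further step to 0.099 comes from moving to an exact test and should not be charged to the plan.

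**The case against.** **Two groups may have been meant.** A two-sample test is valid for comparing the Yes share between two sets of respondents, and this part of the analysis covers patients, caregivers and physiotherapists. Some patient-facing forms are not shown, so that reading cannot be fully excluded. But the sentence names no groups, and the next sentence already sends comparisons with categorical variables to the chi-squared test. The literal reading is the better supported one. The point that stands is that the authors should say what is compared.

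**A flat 17% against 5%.** A reader might infer that the true rate is 17% where 5% was promised. The article promises no level, fixes no n and does not exclude N/A. The 17% is a large-sample value under stated assumptions, and N/A kept in the denominator lowers it. Over the cases shown at nominal 5%, the rate nonetheless stays at about twice nominal or more.

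**The experience objective as a whole.** A reader might also infer that its results are unsafe. The documents do not support that. Frequencies and proportions are planned first and are unaffected, as are the qualitative themes. No stated decision or success criterion hangs on these p-values, and items with overwhelming agreement would be significant under either test.

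**Caregiver item 3.** It is tempting to count its wording as part of the same error. It is a separate flaw in the questionnaire and adds nothing to the false-positive rate. The form also asks for a comment on every question, so the substance of the answer may still be captured.

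**Conclusion.** The concern holds for the test as written. Yes and No on one item are dependent shares of one sample, and the two-sample test overstates the evidence for a difference between them. At an assumed two-sided 5% level with N/A excluded, the false-positive rate is about 17% in large samples and between 11.5% and 23.0% for n from 20 to 300. With 10% to 30% N/A in the denominator it is about 15% to 11%, still more than twice nominal.

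The effect is confined to the tests on experience; the analyses of treatment effects do not use this comparison. It should be fixed before analysis, but it does not threaten the study's main descriptive output.

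Separately, the Yes count for caregiver item 3 cannot be interpreted. If Yes means that something was difficult, it is an unfavourable answer, and a Yes-against-No p-value for that item would have no clear meaning.

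**What to change.** Replace the sentence on the two-sample test as follows:

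- For each item, report the percentage Yes among Yes/No answers with a 95% Wilson interval, and show the number answering N/A separately.
- If a test is wanted, use a one-sample exact binomial test of the Yes proportion against 0.5 and state the significance level. In the enumeration its actual size was 2.1% to 4.6% over the sizes examined from 10 to 1000, never above 5%.
- Keep the two-sample test only for comparing two groups of respondents. If that was the intention, name the groups.

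Reword caregiver item 3 as a true Yes/No question about whether anything was difficult, followed by a request to say what, and report it apart from items where Yes is favourable. If the form can no longer be changed, leave item 3 out of the Yes/No testing and use its comments.

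The cost is a short change to the analysis text and one questionnaire item. No change to design or data collection is needed otherwise. Some items will look less significant than under the planned test.

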Consistency and reliability during the proposed telehealth sessions will be ensured by following the telehealth guidelines set out by the SASP during 2020 and the HPCSA in 2014 and 2020. Participants will be asked to provide feedback for the orthopaedics and NMS subgroup and to complete a questionnaire for the paediatric population to provide their perceptions and experiences of telerehabilitation. For all interactions, attempts will be made to communicate with participants in their language of choice.

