At each follow-up session, the following will be obtained: feedback from the caregiver on the patient’s functional status, the response of the child to the HEP and feedback/concerns from the caregiver, by using the Subjective Assessment Framework. Based on the caregiver’s report, the HEP and advice will be progressed accordingly and referrals made. At the final consultation as determined by the condition of the patient, caregivers will be requested to provide feedback on their perceptions and experiences of telerehabilitation (Appendix 5). If less than satisfactory outcome with telerehabilitation is received, face-to-face sessions will be considered as an alternative to telerehabilitation. Once patients have reached their functional goal, they can be discharged. Feedback from the therapist on the telerehabilitation experience will be collected as shown in Appendix 6.

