### Caregiver questionnaire English

Please answer questions 1 to 10 and give a brief comment and suggestion for all questions.

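### Analysis item 5 names two qualitative sources, and neither covers the comments paediatric caregivers are asked to write on the Appendix 5 questionnaire

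*Protocol article*

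**What the plan says.** The first listed objective covers the experiences of patients and/or caregivers and of physiotherapists. The Protocol article collects these by different routes. In Methods and design, the orthopaedic and neuromusculoskeletal groups give feedback, while caregivers are asked "to complete a questionnaire for the paediatric population to provide their perceptions and experiences of telerehabilitation". The paediatric Procedures place this at the final consultation and name the form: "caregivers will be requested to provide feedback on their perceptions and experiences of telerehabilitation (Appendix 5".

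Appendix 5 opens with the instruction "Please answer questions 1 to 10 and give a brief comment and suggestion for all questions". It has ten questions. Questions 1 to 9 offer Yes, No or N/A, question 10 has a five-level scale, and every question has a field for comments or suggestions.

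Two analysis items deal with experience:

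- Item 4 is quantitative. It gives frequencies and proportions, and then: "The two samples proportions test will be used to compare if there are any differences between the Yes or No responses". A chi-squared test is added for comparisons with categorical variables.
- Item 5 is qualitative: "Qualitative information will be gathered from two sources". The first is "The therapist’s experiences will be collected as positive, negative, challenges and other". The second is described thus: "In the subjective framework of questions, patients are asked a directed open-ended question on their experience of the call and the telerehabilitation sessions". Of the second it says: "The responses will also be categorised into themes that emerge".

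**The concern.** Item 5 does more than stay silent on detail. It gives a number of sources and identifies each one, and the protocol's own caregiver form lies outside both. An analyst who follows it would theme what therapists say and what patients answer to the framework question, and would tabulate the caregivers' ticks. The caregivers' reasons and suggestions, which the form asks for on every question, would have no place in the analysis.

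At stake is the caregiver part of the first objective in a study described as mixed method. The paediatric experience result would be a set of closed-answer percentages without the explanations given alongside them. One question, on what was difficult, would lose its content altogether, and that is the question most directly about barriers to the service.

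**Working it through.** No formula applies, and the plan gives no figure to reproduce. The check is whether any stated analysis reaches the free text on Appendix 5.

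**Inputs.** Sources named in item 5: 2. Questions on Appendix 5: 10, all 10 with a comment field. Closed formats: 9 questions with Yes/No/N/A and 1 with a five-level scale.

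**Step 1: the first source.** It consists of therapists' experiences. The matching form is Appendix 6, which therapists complete. It contains no caregiver text.

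**Step 2: the second source.** It is tied to the subjective framework of questions, not to the questionnaire. The paediatric framework is printed in full as Appendix 4. Its categories are progress and general concerns, functional abilities, physical difficulties in orthopaedic cases, communication, hearing and vision, feeding and growth, orthotics and devices, general coping, and goals set and met. None asks how the caregiver experienced the calls or telerehabilitation. The coping row asks how the caregiver is managing with the child. Appendices 1 and 2 are not shown, but the text assigns them to arthroplasty and low back pain, so they do not bear on the paediatric group.

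**Step 3: the other analysis items.** Item 3, on paediatric effects, summarises categorical variables. Item 4 takes the closed experience answers. Neither mentions free text.

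| Caregiver data on Appendix 5 | Analysis assigned |
|---|---|
| Yes/No/N/A, questions 1 to 9 | Item 4 |
| Five-level scale, question 10 | Item 4 |
| Comments and suggestions, questions 1 to 10 | None |

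**Step 4: count.** Comment fields assigned to an analysis: 0 of 10, so 10 − 0 = 10 per caregiver are unassigned.

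**Step 5: question 3.** It asks what was difficult about the calls and treatment, yet offers Yes/No/N/A boxes. A tick cannot answer a question that begins with what. One could guess that Yes means there was some difficulty, but the form does not say so. Even on that guess the proportion does not say what the difficulty was. The substantive answer can only be in the comment field. So for 10 − 1 = 9 questions the closed answer survives without its reason, and for 1 question the substantive answer itself drops out.

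**The case against.** The strongest reply is that this is omission, not exclusion. No sentence says the comments will be left out, and a condensed article commonly leaves the handling of individual free-text fields to a fuller document. The two sources might also be read as two respondent groups, therapists on one side and patients or caregivers on the other, as in the title of item 4. The first part stands as a limit on the claim: the comments go unanalysed only if the plan is followed as written. The second does not remove the point, because item 5 goes on to tie the patient source to a question in the subjective framework, and the paediatric framework contains no such question.

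Several stronger readings are tempting and should not be drawn:

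- A reader might infer that neither source holds any text from paediatric caregivers. That is not so. Appendix 4 is largely open-ended and records, for example, what is difficult about the home exercises. What it lacks is a question on the calls or on telerehabilitation.
- A reader might infer that the data are lost. They are collected, and the Data management section keeps questionnaire hard copies for 6 years.
- A reader might object that therapists' text starts from four headings while patients' text is themed as it emerges. That is an ordinary choice. No objective requires the groups to be compared under common headings.
- A reader might invoke the Discussion's aim of an in-depth understanding. That sentence concerns the efficacy of telerehabilitation, so it adds nothing here.
- A total number of lost comments cannot be given, because the article states no paediatric sample size. Nor can the free-text streams be counted reliably, since recordings, session notes and diaries also hold narrative and two appendices are not shown.

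**Conclusion.** The point holds in this form: item 5 states a closed count of two sources that omits the free text on the form the protocol uses for paediatric caregivers' experience. Its size is ten comment fields per caregiver with no assigned analysis, one of which carries the only meaningful answer to its question. The closed answers to the other nine questions are still analysed, and the adult groups are untouched. The only statistical result affected is the proportion and any test for question 3, which cannot be interpreted.

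This rests on reading item 5 as printed and on Appendix 4 being the paediatric version of the framework to which item 5 refers. If a fuller document already assigns the Appendix 5 comments to thematic analysis, the gap is in the article only, and its count of sources still needs correcting. The change should be made before coding begins. The defect does not threaten the study as a whole.

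**What to change.** Amend item 5 to name three qualitative sources, adding the comments and suggestions from Appendix 5. Theme them in the same way as the patient responses, and report the themes beside the closed result for the same question. Report question 3 from its text, and take it out of the Yes/No proportions and tests in item 4. The existing coding approaches for therapists and patients can stay as they are.

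The cost is about one or two sentences in the analysis section and some extra coding time. No new data collection is needed, because the form already asks for the comments.
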